**Methods:**

This is a multicenter, open-label, prospective, randomized controlled trial that will be conducted at 3 centers in Tokyo, Japan. Pediatric patients aged 3-10 years with anisometropic, strabismic, or refractive amblyopia will be enrolled. Participants will be assigned 1:1 to a VR app group or a control group. The VR app group will use the VR app at home for 1 hour per day for 6 months. The control group will undergo conventional occlusion therapy with an eye patch for 6 months. Each group will comprise 15 participants (30 participants in total). Ophthalmologic examinations will be performed at baseline and at weeks 4, 8, 12, 16, 20, and 24. The primary endpoint will be the change in the best-corrected visual acuity in the amblyopic eye from baseline to week 12. Secondary endpoints will include changes in best-corrected visual acuity, stereopsis, and ocular deviation through week 24. We will also assess treatment adherence, defined as the ratio of the cumulative actual treatment time to the cumulative prescribed time; record adverse events, and evaluate usability in the VR app group. Longitudinal changes in outcome measures will be analyzed using a mixed-effects model.

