### Sample Size and Statistical Analyses

The primary outcome of this study will be to determine whether the improvement in BCVA from enrollment to 12 weeks in the VR app group is noninferior to the improvement in BCVA from enrollment to 12 weeks in the control group. Based on the assumption that the difference in mean BCVA at 12 weeks between the control and VR app groups will be 0.07 LogMAR [35], the common standard deviation will be 0.14 [36] LogMAR, the noninferiority margin will be 0.10 LogMAR [37], the significance level will be 2.5%, and statistical power will be 90%, a sample size of 24 participants (12 per group) is required [19]. Anticipating a dropout rate of approximately 20%, the target sample size has been set to 30 participants (15 per group).

To assess whether the VR-based program for amblyopia is noninferior to eye patch therapy, the 95% CI for the change in BCVA between 0 and 12 weeks will be calculated for both the control and VR app groups. If the lower bound of the 95% CI for the change in BCVA in the VR app group is greater than that in the control group, the VR-based program for amblyopia will be considered noninferior to eye patch therapy, and the primary outcome criterion will be met.

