For between-group comparisons of BCVA, stereopsis, ocular deviation, and the ratio of total treatment time to the target treatment time, 2-tailed *t* tests or repeated-measures mixed-effects models will be used. Within-group comparisons will be conducted with 2-tailed paired *t* tests, repeated-measures analysis of variance, or repeated-measures mixed-effects models. Reliability and validity evaluations of stereopsis measurements using the VR app compared with the Titmus stereo test administered at clinical visits will be performed using 2-tailed paired *t* tests, Cronbach α coefficients, or intraclass correlation coefficients. The associations between VR gameplay status, ophthalmological examination results, and treatment adherence will be examined using multiple regression analyses or mixed-effects models adjusted for confounding factors. The number of adverse events in the control and VR app groups will be compared using the chi-square test. If continuous variables deviate substantially from a normal distribution, more appropriate methods such as the Mann-Whitney *U* test will be applied. A 2-sided significance level of 5% (*P*<.05) and 95% CI will be used for all analyses. We will not apply multiplicity adjustments across secondary outcomes that represent different endpoint domains. However, when repeated measurements of the same outcome are compared at multiple time points (eg, longitudinal analyses of BCVA), appropriate multiple-comparison adjustments (eg, Bonferroni correction or equivalent family-wise error control) will be applied within that end point family. Primary and secondary analyses will follow intention-to-treat, including all data collected before withdrawal. A per-protocol analysis will be performed as supplementary to assess the robustness of the findings.

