This study has certain limitations. First, despite the explicit inclusion criteria specifying participants with anisometropic, strabismic, or refractive amblyopia and a BCVA of ≤0.5 logMAR in the amblyopic eye, heterogeneity in disease severity, underlying etiology, and associated comorbidities may influence therapeutic outcomes. Second, interindividual differences in age, prior exposure to VR devices, and degree of familiarity may have affected both adherence and therapeutic response, especially during the initial phase of the study. To minimize the influence of such heterogeneity, participants allocated to the VR app group underwent an interim visit at week 2—prior to the first ophthalmologic assessment at week 4—during which VR app usage was reviewed to facilitate the proper continuation of treatment, even among participants with limited prior experience using VR systems. Third, the extended use of the VR app carries the potential risk of adverse effects, including VIMS and asthenopia. Our prior safety evaluation of the VR app in adults revealed no VIMS- or vision-related adverse events [18]. However, data on the long-term use of VR apps in pediatric populations remain limited, and the occurrence of adverse events could potentially affect treatment adherence and diminish the therapeutic efficacy of amblyopia management. Fourth, while amblyopia therapy in clinical settings is generally expected to extend beyond the 6-month duration of this study, this protocol does not permit the evaluation of long-term efficacy, posttreatment sustainability of therapeutic benefits, or the risk of amblyopia recurrence. Upon the completion of this study, an extension study is being conducted to allow interested participants to continue treatment with the VR app. The implementation of such a study with an extended follow-up would facilitate the assessment of long-term therapeutic efficacy and safety, persistence of treatment effects, and the likelihood of amblyopia recurrence. Fifth, the VR app–based stereopsis test used here was newly developed without formal validation. From a visual psychophysics perspective, this task uses a 4-alternative forced-choice design with size-constancy adjustments to reduce monocular cues. However, the extent of monocular cue elimination remains unverified. The floor and ceiling disparity levels of this stereotest are undetermined. Therefore, the stereopsis outcomes should be interpreted as preliminary. We included an in-headset stereopsis measure as it may provide a practical way to assess stereopsis under intervention conditions and enable monitoring between clinic visits, with potential utility for future clinical implementation and remote assessment in telemedicine.

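### The primary noninferiority decision rests on an unadjusted change in each arm; a baseline-adjusted week-12 difference would be more precise and would let children without a week-12 value contribute

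*Protocol article*

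**What the plan says.** The Abstract defines the endpoint: "The primary endpoint will be the change in the best-corrected visual acuity in the amblyopic eye from baseline to week 12". Sample Size and Statistical Analyses then fixes the analysis: "the 95% CI for the change in BCVA between 0 and 12 weeks will be calculated for both the control and VR app groups". Noninferiority is declared from the two intervals under one condition, whose last word refers to the comparator arm: "If the lower bound of the 95% CI for the change in BCVA in the VR app group is greater than that in the control". No covariate, between-group estimate or intermediate visit appears in this rule.

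Three other statements bear on it.
- The same section sets the analysis population: "Primary and secondary analyses will follow intention-to-treat, including all data collected before withdrawal". Per-protocol analysis is supplementary.
- For between-group comparisons, including BCVA, it offers t tests as one option; as the other, "repeated-measures mixed-effects models will be used". The Abstract says "Longitudinal changes in outcome measures will be analyzed using a mixed-effects model". Neither sentence is tied to the noninferiority rule.
- The sample size allows for loss: "Anticipating a dropout rate of approximately 20" percent, so 12 evaluable children per arm become 15 randomised.

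BCVA is measured at baseline and every four weeks to week 24, and age is recorded. The limitations in the Discussion accept that "heterogeneity in disease severity, underlying etiology, and associated comorbidities may influence therapeutic outcomes".

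**The concern.** With about 12 evaluable children per arm, precision is scarce. Subtracting baseline overcorrects for it whenever the correlation between baseline and week 12 is below 1: an arm that starts worse by chance tends to improve more through regression to the mean. Using baseline as a covariate removes that noise and narrows the interval.

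The second issue is internal consistency. A 0 to 12 week change cannot be computed for a child who leaves before week 12. The primary rule gives such a child no way in, while the intention-to-treat sentence says that data before withdrawal are included. The two statements need to be reconciled, and a repeated-measures model is a natural way to do it.

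At stake are some points of power and a clear role for children lost before week 12. The validity of the randomised comparison is not in question.

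**Working it through.** **Inputs from the protocol article** (Sample Size and Statistical Analyses): assumed difference 0.07 logMAR, common SD 0.14, margin 0.10, significance level 2.5%, power 90%, 12 evaluable per arm, 20% dropout, 15 randomised per arm.

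**Assumptions of this check.** The article does not give the direction of the 0.07, whether 0.14 is the SD of change or of week-12 acuity, or the correlation r between baseline and week-12 BCVA. I take VR better by 0.07, 0.14 as the SD of change, one-sided 2.5%, equal variances at baseline and week 12, and r from 0.5 to 0.9.

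**The plan's own figure.** n per arm = 2 × 0.14² × (1.960 + 1.282)² / d², where d is the distance from the true difference to the margin.
- VR better by 0.07: d = 0.17, n = 14.3, so 15 (16 with the t distribution).
- Arms equal: d = 0.10, n = 41.2, so 42.
- VR worse by 0.07: d = 0.03, n = 457.7, so 458.

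None gives 12. Only the first reading comes close, so I use it below. The dropout step is right: 24 / 0.8 = 30.

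**Unadjusted power of a margin-based difference test.** SE = 0.14 × √(2/12) = 0.0572. Noncentrality = 0.17 / 0.0572 = 2.97. With 22 degrees of freedom, power is 81.1%.

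**Effect of baseline adjustment.** With unit variances, Var(change) = 2(1 − r) and Var(adjusted) = 1 − r², so the ratio is (1 + r)/2. I use 21 degrees of freedom and multiply the SE by √(1 + 1/20) for the cost of estimating the slope.

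| r (assumed) | Variance ratio | Reduction | SE | Power |
|---|---|---|---|---|
| unadjusted | 1 | – | 0.0572 | 81.1% |
| 0.5 | 0.75 | 25% | 0.0507 | 89.2% |
| 0.6 | 0.80 | 20% | 0.0524 | 87.2% |
| 0.7 | 0.85 | 15% | 0.0540 | 85.1% |
| 0.8 | 0.90 | 10% | 0.0556 | 83.1% |
| 0.9 | 0.95 | 5% | 0.0571 | 81.0% |

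At r = 0.9 the cost of the covariate cancels the gain.

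**Chance imbalance.** One standard error of the baseline difference is √(2/12) = 0.41 baseline SD. The change score keeps a share (1 − r) of it, with reversed sign. The baseline SD implied by an SD of change of 0.14 is 0.14/√(2(1 − r)). At r = 0.5 the shift is 0.41 × 0.14 × 0.5 = 0.029 logMAR; at r = 0.8 it is 0.41 × 0.221 × 0.2 = 0.018. These shifts are already part of the SE of 0.057.

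**What weeks 4 and 8 add.** For a longitudinal model with baseline, weeks 4, 8 and 12, 20% dropout spread over the three intervals, and compound-symmetry or AR(1) correlation, the variance is about 2% to 6% below that of baseline adjustment in children with a week-12 value. Their main use is to bring in children whose week-12 value is missing.

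**The case against.** The strongest case against is that this is a preference for efficiency. In a randomised comparison an unadjusted change score is unbiased and its interval already allows for chance imbalance, so the 0.018 to 0.029 logMAR shift is ordinary sampling variation. Covariates and missing-data handling are often left to an analysis plan, which is not shown here. Naming heterogeneity as a limitation does not contradict an unadjusted analysis. All of this stands, and it limits the weight of the point. It does not remove it, because the article does more than stay silent: it fixes a particular primary analysis, and that analysis uses the available data less well than it could.

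The size is also open to challenge. If 0.14 is the SD of week-12 acuity, the SD of change is 0.14 × √(2(1 − r)) and unadjusted power is 81% at r = 0.5, 89% at 0.6, 96% at 0.7 and 99% at 0.8. Power is then short only at the low end of the range. Moreover, the power figures describe a test of the difference against 0.10, which the written rule does not perform, so they are not a gain over the rule as it stands.

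A reader might infer stronger things that the article does not support.
- That the primary analysis is confined to completers: no such restriction is stated, and the intention-to-treat sentence points the other way.
- That baseline acuity is ignored: a change score subtracts it.
- That mixed models are reserved for secondary outcomes: the text does not say so, only that no model is linked to the primary rule.
- That leaving out weeks 4 and 8 wastes much precision: the loss is small.

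**Conclusion.** The point holds as a recommendation on precision and consistency. The primary rule uses an unadjusted change in each arm, gives no between-group estimate, and does not show how a child without a week-12 value contributes under the intention-to-treat statement. It does not follow that the comparison is biased or invalid.

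Under the assumptions stated, baseline adjustment lowers variance by 25% to 5% and moves power from 81% to about 89% at a correlation of 0.5, 83% at 0.8, and nowhere at 0.9. The correlation, the meaning of 0.14 and the direction of the 0.07 are all assumed.

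Two larger matters sit in the same section: the decision rule never uses the 0.10 margin, and 12 per arm does not follow from the stated inputs. They need their own correction. The change below would also put the margin into the rule, but it would not repair the sample size.

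**What to change.** Define the primary estimate as the VR minus control difference in amblyopic-eye logMAR at week 12, from a repeated-measures mixed model of weeks 4, 8 and 12 in all randomised children, with arm by visit and baseline BCVA by visit. Higher logMAR is worse, so noninferiority is concluded if the upper limit of the two-sided 95% CI lies below 0.10. Keep the unadjusted difference in change as a sensitivity analysis.

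Say how children without any post-baseline visit are handled; modelling baseline as an outcome with a common mean in both arms would let them contribute. Also say whether 0.14 is the SD of change or of week-12 acuity, and which arm the 0.07 favours.

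The cost is a change of wording before database lock, with no new data. The downside is a few extra parameters in 24 to 30 children, so age should be optional and the covariate list short.

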### Primary Outcome

The primary outcome measure will be that the improvement in BCVA in the amblyopic eye from enrollment to 12 weeks in the VR app group is noninferior to the improvement in BCVA in the amblyopic eye from enrollment to 12 weeks in the control group. This outcome measure will be designed to confirm that the amblyopia treatment effect of the VR-based program is not inferior to that of conventional eye patch therapy. In addition, since previous studies investigating amblyopia treatment using a VR headset have shown a significant treatment effect following 12 weeks of use, comparing BCVA at 12 weeks will enable an efficacy assessment of the VR-based program for amblyopia under standard amblyopia treatment conditions, and thus, the 12-week time point will be adopted [19,34].

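### The non-inferiority rule compares the lower limits of two within-arm confidence intervals and leaves out the 0.10 logMAR margin, so it does not test non-inferiority

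*Protocol article*

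**What the plan says.** Under Primary Outcome, the protocol article says the endpoint is meant to "confirm that the amblyopia treatment effect of the VR-based program is not inferior to that of conventional eye patch therapy". Sample Size and Statistical Analyses repeats the aim: the VR arm's gain is to be "noninferior to the improvement in BCVA from enrollment to 12 weeks in the control group". The inputs for the sample size follow, among them "the noninferiority margin will be 0.10 LogMAR", "the difference in mean BCVA at 12 weeks between the control and VR app groups will be 0.07 LogMAR" and "the common standard deviation will be 0.14" logMAR.

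The next paragraph of that section fixes the analysis: "the 95% CI for the change in BCVA between 0 and 12 weeks will be calculated for both the control and VR app groups". Success is declared if "the lower bound of the 95% CI for the change in BCVA in the VR app group is greater than that in the control" arm; the VR program then "will be considered noninferior to eye patch therapy, and the primary outcome criterion will be met".

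No other section supplies a margin-based comparison. Primary Outcome restates the aim without a rule. The general analysis paragraph names t tests or mixed models for between-group comparisons but does not set any of them against a margin.

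**The concern.** The sample-size paragraph plans one test and the decision paragraph describes another. A non-inferiority test asks whether the confidence interval for the difference between arms excludes a deficit as large as the margin. The written rule departs from this in four ways:

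1. The 0.10 margin does not enter it.
2. No interval for the difference is formed.
3. The outcome depends on each arm's spread as well as its mean. A noisier control arm has a lower limit that is easier to beat.
4. The sign of change is left open. On logMAR a higher value is worse, so week 12 minus baseline is negative when vision improves. On that coding a greater lower bound points to a worse VR result.

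This is the success criterion for the primary outcome. If it is followed as written, the error rate is not the planned 2.5%, and a positive result would not support a claim of non-inferiority.

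**Working it through.** **Inputs.** From Sample Size and Statistical Analyses: margin 0.10, SD 0.14, assumed difference 0.07, significance level 2.5% (read as one-sided), power 90%, 12 evaluable and 15 enrolled per arm. Assumptions made here: the SD of 0.14 applies to the change, changes are normally distributed, and the 0.07 favours VR. The protocol gives no direction for the 0.07.

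**The plan's own figure.** For a test against the margin, n per arm = 2 × 0.14² × (1.960 + 1.282)² / (0.10 + 0.07)² = 14.3, so 15, or 16 with the t distribution. The stated 12 does not reproduce. That shortfall is a separate matter, but it sets the comparator: at 12 per arm a margin-based CI has 81% power, and at 15 per arm 89%.

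**The written rule, change scored as improvement.** Let d be the true VR minus control improvement. The rule passes when

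m_VR − t·s_VR/√n > m_C − t·s_C/√n, that is, when m_VR − m_C > t(s_VR − s_C)/√n.

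The 0.10 is absent. With equal SDs the right-hand side averages zero, so at d = 0 the rule passes half the time at any sample size.

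Normal approximation at n = 12: t(11) = 2.201, and the mean of s is 0.9776σ, so its variance is (1 − 0.9776²)σ².

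- The SE of the mean difference is 0.14 × √(2/12) = 0.0572.
- Random variation in the two SDs multiplies this by √[1 + 2.201² × (1 − 0.9776²)] = 1.102, giving 0.0630.
- At d = −0.10: Φ(−0.10/0.0630) = Φ(−1.59) = 5.6%.
- At d = +0.07: Φ(0.07/0.0630) = Φ(1.11) = 87%.

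With SDs of 0.10 (VR) and 0.18 (control), the threshold shifts in VR's favour by 2.201 × 0.08 × 0.9776/√12 = 0.0497. The SE is √[(0.10² + 0.18²)/12] × 1.102 = 0.0655. At d = −0.10: Φ((−0.10 + 0.0497)/0.0655) = 22%.

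**The written rule, change scored as week 12 minus baseline logMAR.** The comparison of means reverses. With equal SDs, d = −0.10 gives Φ(1.59) = 94% and d = +0.07 gives Φ(−1.11) = 13%.

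Simulation (200,000 to 400,000 trials per setting) agrees with these results. Probability of declaring non-inferiority:

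| True VR effect; SD VR / control | Rule, improvement coding, n = 12 / 15 | Rule, raw logMAR coding, n = 12 / 15 | CI for difference against 0.10, n = 12 / 15 |
|---|---|---|---|
| worse by 0.10; 0.14 / 0.14 | 5.6% / 3.5% | 94% / 97% | 2.5% / 2.5% |
| equal; 0.14 / 0.14 | 50% / 50% | 50% / 50% | 39% / 47% |
| better by 0.07; 0.14 / 0.14 | 87% / 90% | 13% / 10% | 81% / 89% |
| worse by 0.10; 0.12 / 0.16 | 12% / 8% | 98% / 99% | 2.6% / 2.6% |
| worse by 0.10; 0.16 / 0.12 | 2.5% / 1.4% | 88% / 92% | 2.5% / 2.4% |
| worse by 0.10; 0.10 / 0.18 | 22% / 16% | 99% / 99% | 2.6% / 2.6% |
| worse by 0.10; 0.18 / 0.10 | 1.1% / 0.6% | 78% / 84% | 2.7% / 2.6% |

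The unequal SDs are illustrations; the protocol assumes a common SD.

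**A single data set, 12 per arm.** VR mean improvement 0.10 (SD 0.08), control 0.20 (SD 0.28).

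- VR lower limit: 0.10 − 2.201 × 0.08/√12 = 0.049.
- Control lower limit: 0.20 − 2.201 × 0.28/√12 = 0.022.
- The rule declares non-inferiority, although VR improved half as much.
- CI for the difference: −0.10 ± 2.074 × √[(0.08² + 0.28²)/12] = −0.27 to 0.07. It extends past −0.10, so non-inferiority is not shown.

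**The case against.** Five points can be made for the plan.

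- **Sign.** The objective speaks of improvement and the rule treats greater as success, so the natural reading is that positive means better. On that reading the reversal (94% and 13%) does not occur. This is fair, and those figures are conditional on the other coding. Still, the rule itself refers only to a change in BCVA measured on logMAR, and nothing fixes its direction.
- **Size of the excess.** With improvement coding, equal SDs and all 15 per arm contributing, the error is 3.5% against 2.5%, which is modest. Unequal spread can also push it below nominal. Both statements are correct. They show that the error rate depends on which arm happens to be noisier, so it is not controlled.
- **Power.** If VR is better by 0.07, the written rule succeeds in 87% (12 per arm) or 90% (15 per arm) of trials, more often than the margin-based CI at 81% or 89%. This is true under equal SDs, but at 12 per arm the gain comes with an error rate above 2.5%.
- **Exploratory study.** Secondary Outcomes calls the study exploratory, and the article's closing paragraph defers to future confirmatory trials. However, the hypothesis-generating label is applied to the outcomes other than the primary, and Primary Outcome speaks of confirming non-inferiority.
- **Detail left to the SAP.** The rule is stated in full, so this is not an omission. A SAP that followed it would carry the error, and one that departed from it would contradict the published criterion.

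**Conclusion.** The concern holds and must be fixed. As written, the primary criterion uses neither the margin nor an interval for the difference, under either sign of change. With improvement coding and a common SD of 0.14, its false non-inferiority rate at a 0.10 deficit is 5.6% at 12 per arm and 3.5% at 15. Across the illustrative SD pairs it runs from 1.1% to 22% at 12 per arm, where the proper test stays between 2.5% and 2.7%. If change is coded as week 12 minus baseline, the rule favours the worse arm.

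The absence of the margin and of a difference interval is plain from the text and needs no assumption. The percentages rest on normal data and on the SD of 0.14 applying to change. The wider range rests on assumed unequal SDs, and the reversal on the undefined sign.

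**What to change.** Replace the decision paragraph with wording to this effect: *Change is week 12 minus baseline logMAR in the amblyopic eye; negative values are improvement. Non-inferiority is concluded if the upper limit of the two-sided 95% CI for the between-group difference in change (VR minus control) is below +0.10 logMAR.* Use the same statement in the SAP.

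This keeps the protocol's own margin and significance level and returns the error rate to 2.5%. It costs one paragraph, and the change of rule needs no additional data or patients. It does not cure the separate sample-size shortfall: under the stated inputs the corrected test has 81% power at 12 evaluable per arm, and 90% needs 15 (normal) or 16 (t) evaluable per arm. The amendment should be made before database lock, until when Data Management says the investigators have no access to study data; afterwards it could look driven by the results.

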### Study Procedures

Figure 2 illustrates the study enrollment procedure. After obtaining informed consent, pediatric patients will be randomly assigned to either a VR app group, which will undergo amblyopia treatment using the VR app for pediatric patients with amblyopia combined with full refractive correction glasses, or a control group, which will undergo amblyopia treatment based on occlusion treatment with an eye patch combined with full refractive correction glasses [24]. Patients assigned to the VR app group will use the VR app for amblyopia at home for 1 hour per day for 6 months, in combination with full refractive correction glasses. Patients assigned to the control group will follow occlusion therapy with an eye patch for 6 months, also wearing full refractive correction glasses, and the duration of eye patch use will be determined by the prescribing physician. Both groups underwent ophthalmological examinations on the first day of the trial and at weeks 4, 8, 12, 16, 20, and 24. Ophthalmological examinations will include measurements of visual acuity, intraocular pressure, strabismus angle, stereopsis, refractive error, and corneal curvature. Only the VR app group will perform a digital stereopsis test using the VR app once per week and complete a usability questionnaire on the VR app at weeks 2, 12, and 24. The week 2 visit conducted only for the VR app group is intended to confirm that the study participants, particularly those unfamiliar with VR devices, are using the VR app correctly and facilitate their continued appropriate use. Only the control group will record their daily duration of eye patch use in a diary. Study participation will end for both groups after the 24-week visit.

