### VR App–Based Stereopsis Test

In the VR app group, a stereopsis test will be conducted using the VR app (Figure 3). In this test, 4 spheres are projected to both eyes, with 1 sphere placed directly in front of each eye. One of the 4 spheres will be moved forward along a path perpendicular to the viewing direction, and the participants will be asked to identify which sphere moved. When the sphere moves closer, its size decreases, whereas when it moves farther away, its size increases. This feature prevents the detection of sphere movement based solely on changes in size and ensures that the movement cannot be recognized by a single eye on the side of the moving sphere. This stereotest is a newly developed measure that has not yet undergone formal validation. The results of the VR app–based stereopsis test will be compared with those of the Titmus stereo test [28].

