To evaluate the effects of amblyopia treatment in the control and VR app groups, BCVA in the amblyopic eye will be assessed as secondary outcome 1 and stereopsis in the amblyopic eye as secondary outcome 2. To assess the reliability and validity of stereopsis measurement using the VR app, secondary outcome 3 will involve comparing stereopsis in the amblyopic eye measured using the VR app for pediatric amblyopia with that obtained during clinical visits using the Titmus stereo test. To evaluate treatment adherence in the control and VR app groups, secondary outcome 4 will involve assessing the ratio of the total wearing time to the target wearing time. To evaluate the safety of amblyopia treatment using the VR app, secondary outcome 5 will involve comparing the angle of strabismus in the amblyopic eye between the control and the VR app groups. To investigate how VR gameplay status correlates with efficacy and safety, secondary outcome 6 will involve examining the VR gameplay status in the VR app group (including game type, play date or time, play duration, and game settings) in relation to BCVA, stereopsis, treatment adherence, and ocular deviation. Secondary outcome 7 will evaluate malfunctions of the VR app for pediatric amblyopia, secondary outcome 8 will monitor adverse events, and secondary outcome 9 will assess usability in the VR app group. Adverse events will be monitored throughout the trial. Based on our safety evaluation of the VR app in adults, where no visually induced motion sickness (VIMS) or vision-related adverse events occurred [18], the intervention is not expected to pose major safety concerns. However, careful monitoring remains essential in pediatric populations. Possible adverse events include VIMS, asthenopia, diplopia, transient blurring, and headaches. All adverse events reported by participants or observed during clinic visits will be documented and evaluated for severity and relationship with the intervention. Among the secondary outcomes, those related to BCVA, stereopsis, ocular deviation, and treatment adherence (secondary outcomes 1‐4) have been defined as key secondary end points. Since this is an exploratory clinical study, all secondary outcomes other than the primary outcome will be analyzed and interpreted in an exploratory (hypothesis-generating) manner.

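### The methods named for checking the VR stereotest against Titmus are offered as alternatives, and the paired t test or Cronbach alpha used alone cannot show agreement

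*Protocol article*

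**What the plan says.** The purpose is given under Secondary Outcomes: "To assess the reliability and validity of stereopsis measurement using the VR app, secondary outcome 3 will involve comparing stereopsis in the amblyopic eye" with the clinic Titmus result. The methods are given under Sample Size and Statistical Analyses: a two-sided paired t test, "Cronbach α coefficients, or intraclass correlation coefficients". They are joined by *or*; the form of the ICC, limits of agreement and a criterion for acceptable agreement are not given.

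The section on the VR stereotest states: "This stereotest is a newly developed measure that has not yet undergone formal validation". The Discussion adds: "The floor and ceiling disparity levels of this stereotest are undetermined", and calls the stereopsis results preliminary. Only the VR arm takes the test: "Only the VR app group will perform a digital stereopsis test using the VR app once per week". That arm has 15 children, or about 12 after the planned 20% dropout.

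On rank, the article says "secondary outcomes 1‐4) have been defined as key secondary end points", which by number includes outcome 3. The same sentence lists ocular deviation, which is outcome 5, so the rank of outcome 3 is unclear. All secondary outcomes are to be interpreted as exploratory.

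**The concern.** Validating a new measure against an established one raises two questions: is it shifted on average (bias), and how far apart can the two readings be in one child (imprecision)? A paired t test addresses only the first, and a non-significant result in a small sample does not show that the shift is absent. Cronbach alpha describes how consistently items of one scale move together. Applied to two instruments, it depends on their correlation and relative spread, and a constant shift leaves it unchanged. A consistency ICC shares that blindness.

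Because the methods are alternatives, the plan is satisfied by reporting just one of them, and that one may be blind to the fault the test has. Reliability in the sense of repeatability is a separate question, which no comparison of VR with Titmus answers.

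At stake is the only validation of this test that the article describes. The Discussion mentions possible later use for monitoring between visits and remote assessment.

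**Working it through.** The article gives no target or threshold for outcome 3, so there is no figure to reproduce.

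**Inputs from the article:** 15 children in the VR arm, about 12 after 20% dropout; two-sided 5% level. **Assumptions, not in the article:** readings on a log10 arcsec scale, and the SDs stated below.

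**1. Paired t test and imprecision.** When the true mean difference is zero, P>.05 occurs in 95% of trials by construction, whatever the spread of differences. Simulation (20,000 trials, n = 12 and 15, between-child SD 0.45, Titmus error SD 0.15) confirms this:

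| VR test, no mean bias | P>.05 | Median half-width of limits of agreement (log units) |
|---|---|---|
| Good (error SD 0.15) | 95% | 0.40 to 0.41 |
| Very imprecise (error SD 0.6) | 95% | 1.18 to 1.19 |
| Unrelated to Titmus | 95% | 1.27 to 1.28 |

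The P value does not separate the three; the limits of agreement do. By contrast, a very precise pair of tests (error SD 0.05 each) with a bias of only 0.1 log units gives P>.05 in 0.6% of trials or fewer.

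**2. Cronbach alpha and bias.** For two measures of equal variance with correlation r, alpha = 2r/(1+r); bias does not enter.
- r = 0.7: 1.4/1.7 = 0.82.
- r = 0.9: 1.8/1.9 = 0.95.

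In the simulation, median alpha was 0.947 with no bias, a 2-fold bias and a 4-fold bias alike.

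**3. The two ICC forms.** Take SD 0.4 per test, r = 0.9 and bias 0.30.
- Between-child variance: 0.9 × 0.16 = 0.144.
- Error variance: 0.16 − 0.144 = 0.016.
- Variance between methods: 0.30²/2 = 0.045.
- Consistency ICC: 0.144/(0.144 + 0.016) = 0.90.
- Absolute-agreement ICC: 0.144/(0.144 + 0.016 + 0.045) = 0.70.

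In the simulation, the absolute-agreement form was also low for an imprecise test (about 0.51) and an unrelated one (about 0.00). It responds to both faults.

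**4. Can one test be biased and pass both the t test and alpha?** Two settings must be kept apart.
- *Tight differences.* In the setting of step 3, the SD of differences is 0.4 × √(2 × 0.1) = 0.18. At n = 15 the noncentrality is 0.30/(0.179/√15) ≈ 6.5, so the t test misses the factor-of-two bias in under 0.1% of trials. Alpha is 0.95 and shows nothing.
- *Noisy differences.* With an SD of differences of 0.5, the noncentrality is 0.30/(0.5/√15) ≈ 2.3 and the t test misses the same bias in 42% of trials. With SD 0.4 per test, r = 1 − 0.25/(2 × 0.16) = 0.22 and alpha = 0.44/1.22 ≈ 0.36, which would look poor.

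In each setting one method sees a fault that the other misses. The weakness is that either may be reported alone.

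**The case against.** The strongest reply is that nothing in the article would declare the test valid. No alpha or ICC threshold is set, nor is P>.05 said to mean agreement. The article calls the test unvalidated, its range undetermined and the results preliminary; remote use is mentioned only as potential. This stands. A reader might infer that a biased test will be certified as valid and then relied on, but the documents do not support that.

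A reader might also infer that a test misreading by a factor of two would pass every listed check. Step 4 shows otherwise: under these assumptions the t test catches the bias when differences are tight, and alpha or an ICC exposes the noise when they are not. The article does not say that only one method will be reported; it merely permits it.

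The article also promises 95% CIs for all analyses, so the paired comparison would carry a CI for the mean difference. That helps with bias. It is not a statement about individual children: at n = 15 its half-width is 2.145/√15 = 0.55 SDs of the differences, against 1.96 SDs for the limits of agreement.

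Finally, the ICC form, the scale and the handling of repeated visits may properly sit in an analysis plan that is not shown. Agreed; their absence is not the point. Naming the t test and alpha as alternative ways to establish reliability and validity is fixed in this text, and the exploratory label does not make either able to answer that question.

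**Conclusion.** The point holds as a weakness in the chosen methods. No listed method, except an ICC in its absolute-agreement form, covers both bias and imprecision, and the *or* lets one blind method stand for the whole evaluation. The result is a risk of a misleading validation statement, confined to an exploratory outcome in the VR arm. The primary endpoint is untouched.

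Two results need no assumed SD: the 95% non-significance rate at zero mean difference, and the insensitivity of alpha and the consistency ICC to a constant shift. The alpha of 0.95 assumes equal variances and r = 0.9. The ICC of 0.70 further assumes SD 0.4 and bias 0.30 log units. The limits-of-agreement widths and t-test miss rates also rest on assumed SDs. A correction is worth making because it is cheap.

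**What to change.** Replace the list of methods for secondary outcome 3 with:

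1. The Bland-Altman mean difference and 95% limits of agreement, each with a CI, allowing for repeated visits per child. Use a log disparity scale if the VR test yields a disparity threshold; the article gives no score unit, so this must be settled first.
2. A two-way absolute-agreement ICC with its CI.

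Drop Cronbach alpha, and state that a non-significant paired t test will not be read as agreement.

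For repeatability, the weekly VR readings may be used only with a model that allows for change over treatment, or from closely spaced readings with that caveat stated. Stereopsis may truly change under treatment, and a simple comparison of successive readings would count such change as measurement error.

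**Cost:** analysis wording only, with no new visits or measurements. The downside is imprecision. With one reading pair per child, the approximate 95% CI for each limit is ± t × SD × √(1/n + 1.96²/(2(n−1))). At n = 15 this is 2.145 × 0.452 = 0.97 SDs of the differences, and at n = 12 it is 2.201 × 0.508 = 1.12. With an assumed SD of 0.3 log units, that is about ±0.29 and ±0.34 around limits of ±0.59. That uncertainty should be reported.
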